**Discussion:**

Among treatment methods for symptomatic uterine fibroids with the preservation of uterus, laparoscopic uterine artery ligation is expected to have the efficacy like uterine artery embolization, which appeared to be safe for routine use with symptomatic relief. The current study fully recruited in June 2008 and the results will be available in June 2009. If there is no difference of postoperative QOL between laparoscopic uterine artery ligation and laparoscopy-assisted vaginal hysterectomy for the treatment of symptomatic uterine fibroids, the comparison of quality of life between laparoscopic uterine artery ligation and uterine artery embolization will be also needed as a surgical treatment for preserving uterus.

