### Primary outcome

Postoperative QOL 12 months after surgical treatment are evaluated using the European Organization for Research and Treatment of Cancer Quality of Life Questionnaire for Cancer patients (EORTC QLQ-C30) version 3.0., which has been validated to the simplified Korean version [8]. After the evaluation of postoperative QOL, the results will be compared between LUAL and LAVH.

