## Outcome measurements

### Primary outcome

After patients are enrolled and randomized, we interview them using EORTC QLQ-C30 before surgical intervention for the evaluation of preoperative QOL. Since the validity of the EORTC QLQ-C30 has already been demonstrated in Republic of Korea [8], and the authors responsible for the validation recommended its usefulness in the current study, we decided to apply it for the evaluation of postoperative QOL in patients with symptomatic uterine fibroids.

The EORTC QLQ-C30 is a 30-item core-cancer-specific questionnaire-integrating system for assessing the health-related QOL in patients participating in international clinical trials [11]. The questionnaire incorporates five functional scales (physical, role, cognitive, emotional, and social), three symptom scales (fatigue, pain, and nausea and vomiting), a global health and QOL scale, and single items for the assessment of additional symptoms commonly reported by cancer patients (e.g., dyspnea, appetite loss, sleep disturbance, constipation, and diarrhea), as well as the perceived financial impact of the disease and treatment [12]. All items are scored on 4-point Likert scales, ranging from 1 ('not at all') to 4 ('very much'), with the exception of two items in the global health/QOL scale which use modified 7-point linear analog scales [11]. After 12 months, all enrolled patients will be interviewed, and the results of EORTC QLQ-C30 will be compared with preoperative results of it (Fig. 1).

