### Statistical analysis

We will analyze all patients assigned randomly. After informed consent is obtained, blocked randomization is performed by the Medical Research Collaborating Center (MRCC), a central office, in Seoul National University Hospital. The number of participants to be assigned to each of the comparison groups is balanced within blocks. The central office is remote from patient recruitment centers. Thus, participants' details are provided by phone, and the allocation sequence is concealed to individual staffing in the central office until a participant is irreversibly registered.

An intention-to-treat analysis will be performed as the least biased way to estimate intervention effects in the current study. For the primary endpoint, patients with missing EORTC-QLQ-C30 outcomes will be excluded from analysis because they cannot be considered to show specified minimum outcomes of the intended intervention. Analysis of covariance (ANCOVA) will be applied to compare the QOL scores on the basis of EORTC QLQ-C30 between the 2 treatment methods, adjusting for baseline values. After we consider the overall baseline EORTC score, a level of p < 0.05 will be assumed that it indicates imbalance. Thereafter, we will declare the variable to be imbalanced, and then include baseline values of EORTC QLQ-C30 in the ANCOVA to adjust the final results.

Other comparisons between the 2 groups will be made with the use of a two-sided Student's t-test and the Mann-Whitney *U *test for continuous data and the chi-square test for categorical data. The original power calculation requires the enrolled of a total 200 patients to give a power of 90% to detect a difference of 10% in the EORTC QLQ-C30 score at 12 moths (the primary outcome) at the 0.05 significance level.

All independent data such as serious adverse events and recruitment rates will be reviewed by MRCC and the Institutional Review Boards (IRBs) in Seoul National University Hospital, Seoul National University Borame Hospital and Seoul National University Bundang Hospital every 6 months. Moreover, the informal interim analysis for preliminary results will be undertaken, which will inform us whether the current study will be continued or not and maintain the quality of data through balancing baseline data.

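### The informal interim look can include postoperative QOL only after all women are randomised, and nothing keeps its results from those collecting the remaining 12-month interviews

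*Protocol article*

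**What the plan says.** All references are to the protocol article.

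- **Interim look.** Under Statistical analysis, an informal interim analysis of preliminary results is planned, "which will inform us whether the current study will be continued or not". The same sentence gives it a second purpose, which concerns balance of baseline data. It does not name the outcome to be examined, the date, or who performs the analysis.
- **Separate oversight.** The sentence before it reads "All independent data such as serious adverse events and recruitment rates will be reviewed by MRCC" and the IRBs of the three hospitals, every six months. The interim look is added to this review, not made part of it.
- **Primary outcome.** "Postoperative QOL 12 months after surgical treatment are evaluated using" the EORTC QLQ-C30.
- **When and how it is collected.** Under Outcome measurements, the investigators write that "we interview them using EORTC QLQ-C30 before surgical intervention for the evaluation of preoperative QOL". For the later assessment, "After 12 months, all enrolled patients will be interviewed". No QLQ-C30 assessment between these two is described.
- **Calendar.** The abstract states: "The current study fully recruited in June 2008 and the results will be available in June 2009". The timetable gives July 2007 as the start, June 2009 as the end, two years in total and one year per patient.

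**The concern.** An interim look that bears on continuation is normally justified by what stopping would spare: further randomisations, or exposure to an inferior treatment. Here both treatments are single operations, accrual takes as long as the follow-up to the primary outcome, and QOL is not measured in between. The look may therefore be unable to serve that purpose on the primary question.

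The look also has a cost even if the trial continues. The primary outcome is subjective and taken by interview, and no masking is described for those interviews. The only staff described as unaware of assignment are the nurses who present the postoperative pain scale. If between-arm results circulate while 12-month interviews are still being done, knowledge of the trend could influence the remaining answers and bias the final comparison. If the trial stops instead, 12-month outcomes of women already operated on are lost.

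**Working it through.** **1. Calendar.** Inputs: start July 2007, recruitment complete June 2008, one year of participation, primary outcome 12 months after surgery. Twelve months of accrual plus 12 months of follow-up make 24 months, which reproduces the stated two years. The first 12-month QLQ-C30 falls due in about July 2008, after recruitment closed. This does not depend on the shape of accrual, the SD or the significance level.

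**2. What a look would contain.** Assume even accrual of 200 women and surgery at enrolment. Women with a 12-month score at month t = 200 × (t − 12)/12 for t from 12 to 24, and 0 before that.

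| Month from start | Randomised | With 12-month QOL | Interviews to come |
|---|---|---|---|
| 6 | 100 | 0 | 200 |
| 12 (end of June 2008) | 200 | 0 | 200 |
| 15 | 200 | 50 | 150 |
| 18 (end of December 2008) | 200 | 100 | 100 |
| 21 | 200 | 150 | 50 |

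A one-month wait for surgery moves the scores later: 33 at month 15 and 83 at month 18. At no date can a 12-month QOL comparison avert a randomisation.

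**3. Power if the trial stopped.** Take the stated 90% power at 200 patients as given, with a two-sided 0.05 level (the article does not state the sidedness). The standardised effect at full information is 1.960 + 1.282 = 3.242. At information fraction f, power = Φ(3.242 × √f − 1.960).

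- f = 1: Φ(1.282) = 0.90, the plan's own figure.
- f = 0.5: Φ(2.292 − 1.960) = Φ(0.332) = 0.63.
- f = 0.25: Φ(1.621 − 1.960) = Φ(−0.339) = 0.37.

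These are the powers of a trial that does stop there. They are not the expected power of a trial that merely looks.

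**4. Error rate if results circulate and the trial continues.** The plan gives no SD. Reading its 10% difference as 10 points, the stated power implies a standard error of 10/3.242 = 3.08 points. Suppose that no true difference exists, that the look comes at half information, and that the between-arm difference in the remaining half moves by d points towards the sign of the interim estimate. The final estimate then moves by d/2. Simulation with 2 million trials gives the two-sided rejection rate:

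| Assumed d (points) | Move in final estimate | Rejection rate |
|---|---|---|
| 0 | 0 | 5.0% |
| 1 | 0.5 | 7.1% |
| 2 | 1 | 10% |
| 3 | 1.5 | 14% |
| 4 | 2 | 18% |

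Nothing in the article fixes d.

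**The case against.** **The look is never said to use QOL.** This stands. Preliminary results is undefined, and the link to baseline balance suggests a look during enrolment. Operation time, day-2 haemoglobin, three-day pain and early complications would exist by then, and a look at those could have stopped enrolment. A reader might infer that the interim analysis can spare no one whatever it examines. The documents support that only for a look using 12-month QOL. On the other side, complications are to be compared after study completion, serious adverse events already have their own review, and a look without postoperative QOL cannot judge the primary question.

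**The interviewers are not identified.** This also stands. A reader might infer from "we interview them using EORTC QLQ-C30 before surgical intervention" that the people informed by the look are those who conduct the 12-month interviews. That phrase describes the baseline interview; the sentence on the 12-month interview names no interviewer. Read literally, too, what the look conveys may be a decision to continue or not, rather than which arm is ahead. What remains is that no separation is described.

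**MRCC might run it.** Possibly. Adverse events and recruitment are given as examples of what MRCC reviews, so it would be wrong to say that its role is confined to them. The interim look is nevertheless presented as a further item, and no body other than the investigators is named as receiving it.

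**The figures rest on invented scenarios.** Largely right. The 63% and 37% need the trial actually to stop, and the 10% to 18% needs a uniform shift of 20% to 40% of the target difference, following even a trivial trend. Fixed response options make a uniform shift less plausible, without excluding interviewer influence. At 1 point the rate is 7.1%.

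**Conduct of interim looks belongs in the full protocol or SAP.** True of dates, boundaries and procedures, and their absence is not the point here. The article positively states that an informal look informs the investigators' decision to continue. That statement, followed as written, is what needs changing.

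**Conclusion.** The concern holds in a conditional form. From the protocol's own dates, and with no further assumption, a look during recruitment holds no postoperative QOL, and a look that holds it falls after all women are randomised. Such a look can only shorten primary-outcome follow-up. It cannot avert a randomisation.

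The second half is a risk and not a demonstrated bias. It rests on an unmasked, interview-based primary outcome and on the absence of any described barrier between interim results and the remaining interviews, about 100 of 200 at half information under even accrual. Its size is unknown. The error rates of 10% to 18% illustrate an assumed 2 to 4 point shift, and with no shift the rate stays at 5%. The 63% and 37% power apply only if the trial stops at half or a quarter of the data.

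This is separate from adjusting the significance level for the look: a stricter boundary would change neither its timing nor who sees the result. The text should be changed, because the look offers little on the primary question and its removal is cheap.

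**What to change.** In the Statistical analysis section:

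1. Remove the informal between-arm comparison as a basis for deciding whether the trial continues.
2. Keep the six-monthly MRCC/IRB review of serious adverse events and recruitment.
3. State that no between-arm outcome results go to investigators or interviewers until the last 12-month QLQ-C30 is complete.
4. If a comparative look is kept, name the outcomes it uses, have MRCC perform it and hold the results, and let MRCC report only whether there is a concern.

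The cost is one or two sentences, with no additional patients, visits or staff. The investigators lose early sight of preliminary results.

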### Publication policy

The result of the current study will be submitted for publication to peer-review medical journals regardless of whether the outcome is in favor of the objectives in the current study.

### Approval by the Institutional Review Board

We obtained the approval of the IRB of Seoul National University College of Medicine/Seoul National University Hospital for the current study in advance, and the IRB number is H-0704-032-205.

### Registration of clinical trial

The current study has been registered in the Current Controlled Trials with the title "A randomized study of the postoperative quality of life: Laparoscopic uterine artery clipping versus laparoscopy-assisted vaginal hysterectomy for the management of symptomatic uterine fibroids (UTAC trial)" (Trial No. ISRCTN 6790866) [15].

### Trial timetable

#### Trial start

July, 2007

#### Trial recruitment completed

June, 2008

#### Trial end

June, 2009

#### Trial duration

2 years

#### Duration of each patient's participation

1 year

## Discussion

The current study has been designed to compare postoperative QOL between LAUL and LAVH, and to show the similar efficacy of LAUL, compared with LAVH, for the treatment of symptomatic uterine fibroids. Except for LUAL, there are other surgical methods for the treatment of symptomatic uterine fibroids as follows.

Firstly, myomectomy can be performed for reproductive women with uterine fibroids as a cause of infertility and patients with symptomatic uterine fibroids who want to preserve uterus. Although many clinicians have suggested that myomectomy might have more chance of intraoperative bleeding and postoperative transfusion than hysterectomy, some studies have shown that there is no difference of bleeding and transfusion between myomectomy and hysterectomy [16,17]. However, myomectomy can lead to pelvic adhesion which may inhibits conception, and the rate of recurrence is up to 50%. Thus, one third of all patients are known to undergo re-operation for the treatment of uterine fibroids [18].

Secondly, myolysis had been introduced in 1993 as an alternative method for treating symptomatic uterine fibroids. Moreover, it can be performed by laparoscopy or transvaginal approach using thermomyolysis by Nd:YAG laser, cryomyolysis and myoma interstitial thermo-therapy. Although the size of uterine fibroids has been reported to decrease by 30–50%, severe pain by necrosis of them, uterine rupture during pregnancy, uterine abscess and pelvic adhesion can be developed [19,20].

Thirdly, uterine artery embolization (UAE) has also been introduced in 1995 for treating symptomatic uterine fibroids [21]. Early analysis of an open, prospective, voluntary U.S. registry including 3,160 of patients revealed major complications in 5.5% of patients at 30 days, with 0.1% requiring a hysterectomy [22]. Moreover, the National Institute for Health and Clinical Excellence issued guidelines in October 2004, starting that the procedure appeared to be safe for routine use and that the majority of patients have short-term symptomatic relief [23]. However, the technique has some limitations such as postembolization syndrome, the time required to perform the procedure, and radiation exposure for preventing the widespread application.

Thus, LUAL can be efficient for the treatment of symptomatic uterine fibroids, overcoming the complications of UAE. Nevertheless, there is a need for careful assessment of the effects of the procedure on QOL, particularly in comparison with hysterectomy, especially, LAVH.

In conclusion, the current study is meaningful in that we can suggest the results of the comparison of postoperative QOL between LUAL and LAVH. If there is no difference of postoperative QOL between the 2 treatment methods for the treatment of symptomatic uterine fibroids, the comparison of QOL between LUAL and UAE will be also needed as a surgical treatment for preserving uterus.

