## Background

Uterine fibroids are the most common benign uterine tumors. They may be more common in women who are obese, and there appears to be an increased familial incidence [1]. Although fewer than one half of them are estimated to produce symptoms [2], uterine fibroids may cause different symptoms including menorrhagia, intermittent menstrual bleeding, pelvic pain, urinary frequency and constipation.

The management of uterine fibroids is dependent on the patient's age and proximity to anticipated menopause, symptoms, patient preference, and the experience and skills of the clinician. Although non-surgical treatment using gonadotropin-releasing hormone (GnRH) agonist is effective for reducing the size and symptoms of uterine fibroids, surgical treatment is also needed for patients with potential indications such as abnormal uterine bleeding unresponsive to hormone, urinary symptoms or signs such as hydronephrosis and infertility with uterine fibroids as the only abnormal finding.

Among surgical treatments, hysterectomy is a definite method for the treatment of symptomatic uterine fibroids. Especially, laparoscopy-assisted vaginal hysterectomy (LAVH) has more advantages including lesser intraoperative bleeding and shorter hospitalization than abdominal hysterectomy [3]. However, LAVH cannot preserve uterus and can show postoperative complications by the change of pelvic structure [4].

Thus, laparoscopic uterine artery ligation (LUAL) has been introduced in 2001 as an alternative technique for treating uterine fibroids, and significant reduction in the dominant fibroid size (average, 76%) and the uterine volume (average, 46%) were sonographically demonstrated [5]. Thereafter, some studies have reported that LUAL may be effective in relieving the symptoms caused by uterine fibroids, and this procedure can be used in place of hysterectomy [6,7]. Although of these results, there is no study for the comparison of postoperative quality of life (QOL) between LUAL and LAVH.

The current study has been designed to compare the postoperative QOL between LUAL and LAVH, and to evaluate the efficacy of LUAL which can treat symptomatic uterine fibroids with the preservation of uterus.

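### Similarity of LUAL to LAVH is a stated purpose, but the plan has only a test for a difference and no margin or confidence-interval rule, so a non-significant result could not support that conclusion

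*Protocol article*

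**What the plan says.** The first sentence of the main Discussion gives the trial two purposes: to compare postoperative quality of life, and "to show the similar efficacy of LAUL, compared with LAVH, for the treatment of symptomatic uterine fibroids" (LAUL is the article's variant spelling of LUAL).

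The end of the Discussion makes a null finding the trigger for the next comparison, LUAL against uterine artery embolization: "If there is no difference of postoperative QOL between the 2 treatment methods for the treatment of symptomatic uterine fibroids". The Abstract says the same: "If there is no difference of postoperative QOL between laparoscopic uterine artery ligation and laparoscopy-assisted vaginal hysterectomy".

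The Background is neutral: "The current study has been designed to compare the postoperative QOL between LUAL and LAVH, and to evaluate the efficacy of LUAL". So are the Abstract's objectives, the Study design and the Primary outcome.

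Under Statistical analysis the primary comparison is: "Analysis of covariance (ANCOVA) will be applied to compare the QOL scores on the basis of EORTC QLQ-C30 between the 2 treatment methods". The 200 patients are meant to give 90% power "to detect a difference of 10% in the EORTC QLQ-C30 score" at 12 months at the 0.05 level. Sidedness is given only for the remaining outcomes: "Other comparisons between the 2 groups will be made with the use of a two-sided Student's t-test". No equivalence or non-inferiority hypothesis, margin or confidence-interval criterion appears anywhere in the article.

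**The concern.** A conclusion that two operations are similar needs evidence that any difference is smaller than some stated amount. A test of no difference cannot supply it, because a large p-value may reflect either similar arms or an imprecise estimate. Here the test is the only decision tool given, and the conclusion looked forward to is absence of a difference.

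Imprecision would therefore work in favour of that conclusion. Patients with missing questionnaires are excluded from the primary analysis, which widens the interval and makes a non-significant result more likely. At stake is whether a uterus-preserving operation is presented as matching hysterectomy on quality of life when the data leave room for it to be appreciably worse.

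This is not a detail that can be left to an analysis plan. The article itself states both the similarity purpose and the detect-a-difference sample size, and the two do not fit together.

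**Working it through.** **Inputs from the article.** N = 200, power 90%, difference 10%, significance level 0.05 (Statistical analysis). Allocation LUAL:LAVH 1:2, so about 67:133 (Study design).

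**Assumptions.** 10% means 10 points on a 0–100 score, oriented so that higher is better. The primary test is two-sided. The stated 90% power is true. Normal approximation throughout. The article gives no SD.

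**1. The plan's own figure.** Without an SD, N = 200 cannot be reproduced, only back-solved. The SE implied by the stated power is

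SE = 10 / (1.960 + 1.282) = 3.08.

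At 67:133, √(1/67 + 1/133) = 0.1498, so the implied SD is 3.08 / 0.1498 ≈ 20.6. An SD of 20.5 gives 201 patients at 1:2, which agrees with 200 only because the SD was chosen to fit.

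**2. Chance of a non-significant result when LUAL is truly worse by d.**

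P = 1 − Φ(d/SE − 1.960) − Φ(−d/SE − 1.960), with SE = 3.08.

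| True deficit d | P(p ≥ 0.05) |
|---|---|
| 5 | 63% |
| 6 | 51% |
| 7 | 38% |
| 10 | 10% |

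The 63% at d = 5 depends only on the ratio 5/10. In any unit, a deficit of half the planning difference is missed that often if the stated power holds.

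**3. Sensitivity to the SD at 67:133.**

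| SD | SE | P(p ≥ 0.05), d = 5 | P(p ≥ 0.05), d = 10 |
|---|---|---|---|
| 15 | 2.25 | 40% | 1% |
| 20.5 | 3.07 | 63% | 10% |
| 30 | 4.49 | 80% | 40% |

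If design and test were instead one-sided at 0.05, SE = 10 / (1.645 + 1.282) = 3.42, and the figure at d = 5 is 1 − Φ(5/3.42 − 1.645) = 57%. If 20% of questionnaires were missing (an assumption), SE = 3.08/√0.8 = 3.45. The figures become about 69% at d = 5 and 17% at d = 10.

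**4. What a non-significant interval can contain.** The 95% half-width is 1.960 × 3.08 = 6.0. An observed deficit just under 6 is non-significant, yet its interval reaches about 12 points worse, beyond the trial's own planning difference.

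**5. What an interval rule would achieve.** The probability that the lower 95% limit excludes a margin M when the arms are equal is Φ(M/SE − 1.960).

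| Margin M | Power, SE 3.08 |
|---|---|
| 10 | 90% |
| 7.5 | 68% |
| 5 | 37% |

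The 90% at M = 10 restates the power claim and is not independent evidence that 200 is enough. At 67:133 it is 99% for SD 15 and 61% for SD 30. With M = 10, a true 6-point deficit would pass with probability Φ(4/3.08 − 1.960) = 25%, compared with 51% for a non-significant difference test.

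**The case against.** The strongest reply is that the formal aims are neutral. The Abstract, Background, Study design and Primary outcome speak of comparing and evaluating. Similarity as a purpose appears in one Discussion clause, where it attaches to efficacy, and most efficacy measures (symptom score, volumes, bleeding) are secondary outcomes. This stands as far as it goes, so the trial should not be described as a whole as an equivalence trial. But the no-difference sentences in the Abstract and the Discussion are explicitly about quality of life, the primary outcome.

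A reader might infer that the article announces it will take p > 0.05 as proof of similarity, or that LUAL would be adopted on that basis. It says neither. The p-value reading follows from putting the no-difference sentences beside an analysis section that supplies only significance tests, and the only stated consequence is a further study. The article also commits to submitting the results whatever their direction.

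A reader might also infer that the trial is likely to miss a large deficit. At the planning difference the risk is the nominal 10% if the power claim is right. The exposure is to smaller deficits, or to a larger SD or missing data.

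Finally, the figures rest on a back-solved SE, and a difference chosen for detection is not automatically an acceptable margin. Both points stand. A margin of 10 needs its own clinical justification, and an interval rule would not cure an insensitive questionnaire. The mismatch itself needs none of these figures.

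**Conclusion.** The point holds in a limited form. The article states a similarity purpose and builds its next step on finding no difference in quality of life, while its analysis and sample size address only detection of a difference. A non-significant result would not support that conclusion.

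On the stated assumptions, a true LUAL deficit of half the planning difference would be non-significant about 63% of the time, with a range of about 40% to 80% over assumed SDs of 15 to 30. The mismatch is certain from the text. Its size is conditional, because the SD, the meaning of 10% and the sidedness of the primary test are not given. The planned estimate and data are unaffected; what has to change is the inference drawn from them.

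**What to change.** Report the baseline-adjusted LUAL minus LAVH difference with its 95% CI as the primary result. Before the final analysis, and without sight of comparative results, state that:

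- similarity, in the sense of LUAL not being worse, is claimed only if the lower limit excludes a prespecified, clinically justified margin on a named QLQ-C30 score;
- a CI that includes both 0 and the margin is reported as inconclusive;
- no similarity or no-difference conclusion is drawn from p > 0.05 alone.

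The planning difference of 10 is the candidate margin that the existing size can support: about 90% power if the arms are equal and the stated power holds, against about 37% at a margin of 5. It should be adopted only with a clinical argument for it.

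If no margin can be justified, remove the similarity and no-difference conclusions from the Abstract and Discussion and report only the estimate and CI.

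The cost is wording plus the work of justifying a margin. Recruitment was completed in June 2008 and the trial ends in June 2009, so the rule can be set without new patients. The small downside is that some non-significant results must be reported as inconclusive.
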